## Abstract

**Background:**

In the past decade, interest in researching nursing practice environments has increased considerably. Multiple studies have highlighted that substantial benefits result from enhancing these environments. A strong association has been established between the nursing practice environment and key factors such as professional satisfaction, safety climate, staff retention, and the quality and safety of care delivered.

**Aim:**

To evaluate the effectiveness of the Positive Nursing Practice Environment Promotion Programme (PPAPEP) in improving patient safety in primary health care.

**Design & setting:**

A randomised clinical trial will compare changes in nurses' perceptions of the safety climate and nursing practice environment in primary healthcare units. The sample will include at least 34 nurses participating in the programme and currently working in primary healthcare units. The sociodemographic and professional characteristics of the participants will be analysed, and stratified randomisation will be conducted.

**Method:**

The intervention group will participate in the PPAPEP, consisting of six training sessions, each lasting 3 hours. The programme’s goal is to empower nurses by providing knowledge about what constitutes a positive nursing practice environment and equipping them with tools to improve their practice environment. The outcomes of the intervention will be assessed both at the end of the programme and 3 months after its conclusion.

**Conclusion:**

We anticipate that this study will provide valuable insights into the effectiveness of a capacity-building programme targeted at nurses and its impact on their perceptions regarding the safety climate and nursing practice environment.

## How this fits in

Positive nursing environments play a crucial role in enhancing care quality, safety, and professional wellbeing. The Positive Nursing Practice Environments Promotion Programme (PPAPEP) is a validated programme to improve nursing practice environments. Conducting a clinical trial to assess the effectiveness of PPAPEP is essential to understand its impact on the safety climate and practice environments. The results of this study may provide definitive and reliable evidence for strategies and future nursing practice improvements, and may support the development of institutional policies to improve nursing care.

## Introduction

Nursing practice environments (NPE) have gained significant interest owing to their impact on patient outcomes, professional wellbeing, and institutional performance.^
1–3
^ Communication and collaboration among professionals are vital for patient safety, reducing errors, and adverse events.^
4–6
^ Additionally, the NPE plays a crucial role in shaping clients’ perceptions of care quality, with positive environments associated with increased client satisfaction regarding care safety.^
5,7–10
^ A positive NPE is also linked to improved nurse motivation, satisfaction, and retention.^
11–17
^ Workplaces with adequate resources, balanced workloads, and meaningful professional recognition reduce stress, burnout, and the intention to leave the profession, while ensuring greater professional safety and wellbeing.^
18–24
^ NPE also influence institutional indicators, improving health outcomes, pain management, and reducing falls, infections, sepsis, and pressure ulcers.^
5,7,25,26
^ Additionally, they mitigate absenteeism and turnover, improving institutional productivity and efficiency.^
19,23
^

Given this broad range of outcomes associated with positive NPE, it is essential to define this specific concept. A *'positive nursing practice environment'* refers to a workplace that facilitates the delivery of high-quality care, supports healthcare professionals, encourages their involvement in decision making, and promotes effective communication and collaboration.^
27
^ Effective communication, collaboration, trust, and transparency between healthcare professionals, patients, and families are essential for reducing errors and adverse events.^
28,29
^ A favourable safety climate, well-established safety policies, and a secure environment for professionals help minimise conflict-induced errors, promote the safety of both patients and healthcare professionals, and create a positive cycle that enhances care quality, client satisfaction, institutional success, and nurses' wellbeing.^
23,30–32
^

Considering the relevance of NPE and their broad impact, developing and implementing strategies to improve these environments is essential.^
4,19
^ The literature identifies various strategies designed to improve aspects of nurses' work environments; however, these are often isolated measures.^
18
^ Given the scarcity of broad strategies addressing multiple domains of the NPE, we developed Positive Nursing Practice Environments Promotion Programme (PPAPEP), a multicomponent programme designed to promote nurses’ education on what constitutes a positive NPE and provide them with tools to improve their work environment. It was developed based on characteristics or variables influencing NPE, the attributes of positive NPE, and their associated outcomes. This programme was validated through a Delphi study, in which experts recognised in the field assessed and refined the programme.^
33
^ The programme’s contents are presented in Table 1.

**Table 1. table1:** Content of the PPAPEP

Session	Content
1)	Presentation of the PPAPEP. Characteristics and variables related to clients and professionals that contribute to a positive nursing practice environment
2)	Characteristics and variables related to institutions that contribute to a positive nursing practice environment
3)	Attributes of a positive nursing practice environment
4)	Outcomes of a positive nursing practice environment related to professionals
5)	Outcomes of a positive nursing practice environment related to institutions and clients
6)	Group dynamics to consolidate the knowledge acquired throughout the PPAPEP. Conclusion of the PPAPEP

PPAPEP = Positive Nursing Practice Environments Promotion Programme

The final version of the programme, improved through expert input, comprises six sessions that focus on essential themes, including factors influencing clients and healthcare professionals, organisational dimensions, the features of a positive NPE, and its outcomes.^
33
^ The high participation rates and positive responses from the expert panel highlight the programme’s significance and potential impact. The programme’s active-learning approach facilitates reflection and discussion, enhancing communication, teamwork, and collaboration. Delivered through presentations, videos, and interactive exercises, PPAPEP is designed to enhance work environments and perceptions of safety climate. This randomised controlled trial (RCT) aims to evaluate the effectiveness of the PPAPEP in enhancing the perceptions of primary healthcare nurses regarding safety climate and the NPE. It represents the first RCT to test the PPAPEP, potentially strengthening the evidence base on the relationship between the work environment and professionals' perceived safety climate. Additionally, it seeks to provide evidence of the programme’s effectiveness in promoting a positive NPE, guiding institutional strategies, policies, and future research.

## Method

### Study design and settings

This randomised, controlled, and parallel clinical trial will be conducted with investigator and participant blinding (double-blinding). Participant recruitment took place between September and October 2024 in a group of health centres within a local health unit in northern Portugal. This protocol follows the Standard Protocol Items: Recommendations for Interventional Trials (SPIRIT) guidelines^
34,35
^ and the extension for reporting results in clinical trial protocols.^
36
^ Additionally, the trial will adhere to the Consolidated Standards of Reporting Trials (CONSORT) guidelines for clinical trials.^
37
^ The study has been registered on the ClinicalTrials.gov platform with the ID: NCT06762015.^
38
^

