### Allocation, randomisation, and blinding

Participants will be allocated into two groups (intervention and control) and stratified randomisation will be performed to ensure homogeneity between the groups (1:1). Stratification will consider participants’ self-assigned codes along with sociodemographic and professional characteristics such as sex, age, educational background, professional category, total professional experience, experience in primary health care, and the type of unit where they work. Stratified randomisation will be executed using RANDOM.ORG by an independent researcher uninvolved in the PPAPEP intervention or data analysis, because it offers true random numbers that are for many purposes better than the pseudo-random number algorithms typically used in traditional computer statistical software. Regarding the randomisation during each evaluation point, questionnaires will be completed by participants, sealed in opaque envelopes labelled with the respective evaluation moment ('EM0', 'EM1', 'EM2, or 'EM3'). After the final evaluation moment ('EM3'), the questionnaires will be selected based on the administration timeline illustrated in Figure 1. This approach enables participants to choose their preferred day and time for sessions without compromising group homogeneity or randomisation. It also minimises selection and information bias by ensuring that neither the researcher nor the participants are aware of their allocation until data collection is complete. Assessments during the intervention were conducted using self-administered questionnaires, and participants were instructed not to share session information with others.

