### Intervention group

The intervention group will participate in the PPAPEP, which will be delivered in-person by a trained member of the research team in a designated room within the study site. The evaluations for this group will occur at pre-intervention ('EM0'), post-intervention ('EM2'), and 3 months' post-programme ('EM3'), as shown in Figure 1.

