### Control intervention

For the control group, evaluations will be conducted at pre-intervention ('EM0') and before the intervention sessions ('EM1'). Although they will eventually participate in the programme, only evaluations preceding the intervention will be considered.

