### Data analysis

Following the CONSORT guidelines,^
37
^ a flowchart outlining participants’ progression throughout the study will be created. This will include information on sample size, reasons for exclusions, and participant dropouts.

Data analysis will be performed by the research team, with preliminary steps including verification of data discrepancies, potential biases, anomalies, incomplete or missing data, as well as assessments of distribution normality, linearity, and homoscedasticity. These steps ensure compliance with prerequisites for subsequent statistical analyses.

Demographic and professional characteristics of participants will be analysed using descriptive statistics. This will involve measures of central tendency, variance metrics, frequency charts, and 95% confidence intervals for all subgroups.

The analysis will include group comparison tests appropriate for the type of variable under study. A univariate analysis will assess each variable before and after the intervention. Bivariate analyses will examine correlations between dependent and independent variables, while multivariate analyses will explore interactions and relationships among them.

Primary outcomes will focus on participants’ perceptions of the NPE and safety climate in primary healthcare settings. The Student’s *t*-test will be used to compare group mean values, and the paired *t*-test will examine changes within groups. Effect size interpretations will use Cohen’s D index, categorised as small (0.2–0.49), moderate (0.5–0.8), or large (>0.8).^
41
^

Multivariate analysis will include linear regression for dependent variables such as nurses' perceptions of the practice environment and safety climate in primary health care. If assumptions of normality, homoscedasticity, and variable independence are not met, variable transformation will be considered. After regression analysis, the adequacy of the model in representing the observed data will be evaluated, along with the possibility of changes in variable effects.^
42
^

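### The envelope scheme can hide which group a nurse will be counted in, but not whether the nurse has been trained, so the double-blinding and information-bias claims do not hold

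*Protocol article*

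**What the plan says.** Study design and settings describes the design without qualification: the "clinical trial will be conducted with investigator and participant blinding (double-blinding"). Allocation, randomisation, and blinding explains the mechanism. Nurses complete questionnaires at each evaluation moment, the sheets go into opaque envelopes marked EM0 to EM3, and the sheets to be used are picked out only after EM3. Of this scheme the article says: "It also minimises selection and information bias by ensuring that neither the researcher nor the participants are aware of their allocation until data collection is" finished.

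The programme is described in the abstract as "consisting of six training sessions, each lasting 3 hours", and under Intervention group as "delivered in-person by a trained member of the research team in a designated room within the study site". That arm is evaluated at EM0, EM2 and EM3. For the control arm, "evaluations will be conducted at pre-intervention ('EM0') and before the intervention sessions ('EM1"). Controls take the programme later, but only their ratings from before it count. Outcomes evaluation and Data analysis make both primary outcomes the nurse's own perceptions, of the practice environment and of the safety climate, on questionnaires that the nurses fill in themselves.

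**The concern.** When an outcome is self-rated, the participant is the outcome assessor. Information bias in such a rating arises from what the rater knows about their own treatment, not from which group label a researcher will later attach to the sheet. Here the treatment is 18 hours of overt group training (6 × 3 hours). According to Table 1, the sessions cover what a positive practice environment consists of and what it produces, which is close to what the scales ask the nurse to rate. Expectation or a wish to please could therefore alter ratings after the programme without any change in the workplace.

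What is at stake is how a positive result is read. A reader told that the trial was double-blind and that information bias was minimised would not discount for this. Strengths and limitations names prior awareness and dropout as sources of bias, but not unblinded self-assessment.

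**Working it through.** **Step 1. Which scores are used, and what the rater knows.** From Intervention group, Control intervention and Table 2:

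| Moment | Arm whose scores are used | What the rater knows |
|---|---|---|
| EM0 | both | not yet trained |
| EM1 | control | not yet trained |
| EM2 | intervention | has just completed the programme |
| EM3 | intervention | completed it 3 months ago |

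After baseline, arm and known training status coincide for every score that enters a comparison. Figure 1 is not shown. The table does not need it, because the mapping is the same whether controls simply train later or all nurses follow one timeline and sheets are selected afterwards.

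**Step 2. What the envelopes can hide.** Late selection can hide nominal allocation, that is, which of a nurse's sheets will be used. It cannot hide attendance from the nurse, or from the team member who delivers the sessions. The article's claim about information bias needs the second kind of concealment and describes only the first.

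**Step 3. The plan's own figure.** The only related number is the sample size, which does not depend on blinding. For one paired sample with effect size 0.5 and two-sided α 0.05, exact power is 0.795 at n = 33 and 0.808 at n = 34. The stated 34 therefore reproduces, and nothing here corrects it.

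**Step 4. Illustration of size.** The documents give no size for reporting bias, so the shifts δ are assumptions. Inputs: 17 per arm (Sample size), two-sided α 0.05, no true effect, and trained nurses' ratings shifted by δ.

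- Between arms (intervention EM2 against control EM1, δ in SDs of the score): df = 2 × 17 − 2 = 32, noncentrality = δ√(17/2) = 2.915δ.
- Within the intervention arm (paired t-test, δ in SDs of the change): df = 16, noncentrality = δ√17 = 4.123δ.

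| δ | Between arms: noncentrality | Rejects | Within arm: noncentrality | Rejects |
|---|---|---|---|---|
| 0.1 | 0.29 | 5.9% | 0.41 | 6.7% |
| 0.2 | 0.58 | 8.7% | 0.82 | 12.1% |
| 0.3 | 0.87 | 13.6% | 1.24 | 21.4% |

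The nominal rate is 5%. On the paired scale, on which the article's effect size was entered, a shift of 0.2 is 0.2/0.5 = 40% of the effect that the trial is planned to detect.

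**The case against.** Several points on the other side stand.

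- **Concealing the nominal group may be real and useful.** If every nurse is eventually trained and sheets are selected only after EM3, a nurse may not know which group they will count in. This can limit reactions to being labelled a control, and selective handling during collection. A reader might infer that the scheme protects against nothing. The documents do not support that.
- **No blinded analyst is promised.** A reader might infer that investigator blinding is broken because the EM label gives away the arm and, in the article's words, "Data analysis will be performed by the research team". But the allocation section limits concealment to the period of data collection, and analysis comes later. Table 2 marks both scales at all four moments without a split by arm, so during collection an EM1 or EM2 envelope may hold sheets from both arms. The label identifies the arm only after selection. Nor does the article say that the person who trains also analyses.
- **Other safeguards exist.** Participants are coded, questionnaires are anonymous, and the randomisation is done by someone outside both delivery and analysis.
- **Direction and size are assumed.** Training on what a good environment looks like could also make nurses more critical. At 0.1 SD the between-arm inflation is under one percentage point.
- **Exposure to overt training cannot be masked.** The lack of masking is not a fault in conduct. It is, however, the reason why the article should not claim masking.

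None of this rescues the two statements at issue. Participant blinding is claimed without qualification, and information bias is said to be minimised, while every rating used after baseline comes from someone who knows whether they have been trained.

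**Conclusion.** The point holds in this form: the article claims a property that its own design does not have. Participants know their exposure when they rate both primary outcomes, the trainer knows it too, and the envelope scheme conceals at most nominal allocation until data collection ends. This follows from the text alone and does not depend on the illustration.

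The rejection rates of about 6%, 9% and 14% between arms rest on assumed shifts of 0.1, 0.2 and 0.3 SD, no true effect and 17 per arm. They show what such a bias could do, not what it will do. A shift towards the hypothesis is plausible, but the documents do not establish it. The stronger inference, that the analyst is improperly unblinded, is not supported, because the article does not expressly promise a blinded analyst. The tests and the sample size are unaffected by this point. The description and the interpretation must change.

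**What to change.** 1. In Study design and settings, remove the double-blinding statement. Say that participants and the trainer are not blind to exposure.
2. In Allocation, randomisation, and blinding, remove the claim about information bias. State what is concealed (nominal allocation), from whom, and until when (the end of data collection).
3. In Strengths and limitations, add unblinded self-assessment of both primary outcomes as a limit on any positive result.

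These are wording changes in three sections. They remain possible although recruitment is over, and the only loss is the double-blind label.

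Optionally, as an inexpensive improvement and not the correction of an error, the analysis could be masked. The independent researcher who ran the randomisation would give an analyst who did not deliver the sessions only the EM0 score and the first score after baseline (EM1 or EM2), under neutral arm codes. EM3 and the EM labels would be withheld until the primary comparison is locked. Holding back EM3 is essential: the intervention arm has two evaluations after baseline and the control arm one, so neutral codes alone would reveal the arm. The cost is one recoding step.

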### Hypotheses

This study aims to test the following two main hypotheses:

the PPAPEP improves nurses' perceptions of the safety climate in primary healthcare units; andthe PPAPEP enhances nurses’ perceptions of their NPE in primary healthcare settings.

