### Sample size

Considering the study’s objective, we calculated the sample size using G*Power software (version 3.1.9.6) with a two-tailed test to compare two dependent means (Student’s *t*-test). The parameters used included an effect size of 0.5, a significance level (α) of 0.05, and a statistical power (1-β) of 0.80. The calculation suggests a minimum total sample size of 34 participants (17 participants per group). The allocation ratio between the groups will be 1:1. Thus, we aim to recruit at least 34 nurses working in primary healthcare units who are interested in and agree to participate in the study.

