### Outcomes evaluation

Participants will complete a sociodemographic questionnaire, and the programme’s effectiveness will be assessed using two instruments: the shortened version of the Scale for the Environments Evaluation of Professional Nursing Practice (SEE-Nursing Practice)^
39
^ and Safety Attitudes Questionnaire (SAQ) — Short Form.^
40
^

The SEE-Nursing Practice consists of 59 items across three subscales: structure (29 items); process (19 items); and outcome (11 items). Participants rate each item on a five-point Likert scale (1: never to 5: always). Higher scores indicate a more favourable NPE for care quality and professional wellbeing. Scores are interpreted as follows:<35% (unfavourable), 35–55% (moderately favourable), 55–75% (favourable), and>75% (very favourable).^
39
^

The SAQ — Short Form 2006 assesses healthcare professionals' perceptions of patient safety attitudes. It has been previously validated and culturally adapted to the context in which the study will be conducted.^
40
^ The SAQ — Short Form 2006 comprises six dimensions, addressing organisational factors, work environment factors, and team factors, with a total of 30 items. Participants respond to each item using a five-point Likert scale ('strongly disagree' to 'strongly agree'). The final score ranges from 0–100, where 0 represents the worst perception and 100 the best perception of the safety climate.^
40
^ The timing of the outcome measures and data collection evaluation moments are detailed in Table 2, following SPIRIT guidelines and the extension for reporting trial protocol outcomes.^
36
^

**Table 2. table2:** Outcome measures and data collection evaluation moments

Activity	Study period					
	T – 1 (Pre-allocation)	EM0 (baseline)	EM1 (pre-intervention)	Intervention period	EM2 (post-intervention)	EM3 (follow-up)
Enrollment						
- Participants' information	X					
- Participants express interest in PPAPEP	X					
- Participant consent	X					
- Random group allocation		X				
Intervention: PPAPEP			—	—	—	—
Outcomes						
Data collection:						
- Demographic and professional data	X					
- Scale for the Environment's Evaluation of Professional Nursing Practice — Shortened Version		X	X		X	X
- Safety Attitudes Questionnaire — Short Form		X	X		X	X
- Qualitative data from participants’ knowledge during intervention				X		

EM = evaluation moment. PPAPEP = Positive Nursing Practice Environments Promotion Programme

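### Two equal primary outcomes get both between-group and within-group tests, and the article does not say which test or rule decides effectiveness

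*Protocol article*

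**What the plan says.** All places are in the protocol article.

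- **Hypotheses:** "This study aims to test the following two main hypotheses", one on safety climate and one on the nursing practice environment. Neither is ranked above the other.
- **Outcomes evaluation:** "effectiveness will be assessed using two instruments", the SEE-Nursing Practice scale and the SAQ Short Form.
- **Data analysis:** "Primary outcomes will focus on participants’ perceptions of the NPE and safety climate in primary healthcare settings". The next sentence gives these outcomes a Student's t-test between groups and a paired t-test within groups. Neither is called decisive, and no time point is singled out.
- **Intervention group and Control intervention:** the intervention arm is assessed at EM0, EM2 and EM3. The control arm contributes EM0 and EM1 only.
- **Sample size:** a "two-tailed test to compare two dependent means", with effect size 0.5 and "a significance level (α) of 0.05, and a statistical power (1-β) of 0.80", giving 34 in total, 17 per group. This is the only place where an alpha appears.
- **Aim (Abstract) and Introduction:** the purpose is expressed as the effectiveness of the programme, a single idea that spans both scales.

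**The concern.** The article fixes two primary outcomes and two kinds of test for each, but not how the results combine into a statement about effectiveness. That leaves room to rest the conclusion on whichever result turns out significant. Two things are at stake.

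The first is chance error. With several tests at 0.05 and a rule that any one suffices, 5% is no longer the error rate of the overall conclusion.

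The second is what a paired test shows. A pre-post change in the intervention arm has no control, so it picks up any shift over time as well as any programme effect. This is a live possibility here. The paired test is the one the trial was sized on, and the control arm has no analysed measurement at EM3. Within-group change from EM0 is therefore the natural way to present the 3-month result.

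**Working it through.** **Inputs from the article:** two primary scales; alpha 0.05 two-sided; effect size 0.5; power 0.80; 34 in total, 17 per group; intervention at EM0, EM2, EM3; control at EM0, EM1.

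**Assumed, because the article does not give them:** correlation between the scales, 0 to 0.9; correlation between time points, 0.5 and 0.7; normal scores.

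**1. The plan's own figure.** For one paired t-test, the normal approximation gives n = ((1.960 + 0.842)/0.5)² = 31.4. The noncentral t gives 33.4, rounded up to 34, with power 0.808 at 34 pairs (0.795 at 33). The stated 34 is reproduced, as 34 pairs for one paired test on one outcome.

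**2. Two between-group tests, either one sufficing.** If independent, 1 − 0.95² = 0.0975. With correlated scales (bivariate normal simulation):

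| Between-scale correlation | Any p<0.05 | Any p<0.05 in the favourable direction |
|---|---|---|
| 0 | 0.098 | 0.049 |
| 0.3 | 0.095 | 0.048 |
| 0.5 | 0.091 | 0.045 |
| 0.7 | 0.083 | 0.042 |
| 0.9 | 0.071 | 0.035 |

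The nominal values are 0.05 and 0.025, so inflation is about 1.4 to 1.95 times.

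**3. Adding intervention-arm paired tests on both scales** (simulated t-tests, 17 per arm, no change in either arm, 20,000 runs per setting):

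| Tests that count | Independence formula | Simulated, any p<0.05 | Simulated, favourable direction |
|---|---|---|---|
| 2 between + 2 paired EM0–EM2 (four) | 1 − 0.95⁴ = 0.185 | 0.14–0.18 | 0.07–0.10 |
| as above + 2 paired EM0–EM3 (six) | 1 − 0.95⁶ = 0.265 | 0.19–0.26 | 0.10–0.14 |

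These cover chance error only. The simulated null has no drift over time; with drift, the paired tests would reject more often still.

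**4. Other success rules.** If both scales must be significant, the error for the joint claim cannot exceed 0.05. If each hypothesis is reported only as its own claim, each keeps 0.05.

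**5. What each rule does to power.**
- Alpha of 0.025 per scale, on the article's own paired calculation: 40.6, so 41 pairs are needed. Power at 34 pairs falls from 0.81 to 0.71.
- Both scales required, 34 pairs: 0.808² = 0.65 if the scales are independent, and higher if they are correlated.
- Between-group t-test, d=0.5, 17 per arm: power 0.29 at 0.05 and 0.20 at 0.025. Power of 0.80 would need about 64 and 78 per arm.
- Baseline adjustment raises the effective effect size to 0.5/√(1 − ρ²), where ρ is the correlation between baseline and outcome. At ρ = 0.5 this is 0.577, with power 0.37 at 0.05 and 0.27 at 0.025. At ρ = 0.7 it is 0.700, with power 0.51 and 0.39.

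**The case against.** The strongest reply is that this argues from silence. Only a condensed article is shown, and a multiplicity procedure or success rule commonly sits in an analysis plan. That stands: the absence of a named procedure is not by itself an error.

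Three further points also stand.

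- A reader might infer that each hypothesis is tested at 0.05 and that a win on either proves the programme effective. The article says neither. Its 0.05 belongs to the sample-size calculation, and the two hypotheses are joined by a plain conjunction.
- A reader might infer that the false-positive rate is roughly doubled or worse. Doubling needs nearly independent scales, whereas these are two perception questionnaires completed by the same nurses. The larger figures arise only if paired tests count as evidence of effectiveness, which the article neither says nor rules out.
- Both hypotheses are directional. A false claim of benefit needs a result in the favourable direction, which is about 3.5–5% for the two between-group tests.

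What does not fall away is the text that is present. It attaches controlled and uncontrolled comparisons to the same primary outcomes on an equal footing, and it sizes the trial on the uncontrolled kind. An analysis plan could resolve this only by choosing among the tests that the article leaves level.

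**Conclusion.** The point holds as a failure to fix the decisive comparison and the success rule for two equal primary outcomes. It is not a demonstrated doubling of the error rate.

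The size depends on the rule eventually used: about 7–10% if either between-group test suffices, about 19–26% (10–14% in the favourable direction, against 2.5%) if paired tests at EM2 and EM3 also count, and no inflation under a both-must-succeed or separate-claims rule. The ranges rest on assumed correlations and on a null with no change over time.

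The more important half is the status of the within-group tests. If they may support effectiveness, uncontrolled change can carry the conclusion whatever alpha is used. The choice between Holm and another rule is more open to debate. It should be settled before the data are analysed.

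**What to change.** In Data analysis:

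1. Name as the only confirmatory tests the EM0-adjusted between-group contrast, intervention at EM2 versus control at EM1, on the SAQ total and on the SEE-Nursing Practice total. Confirm against Figure 1, which was not available for this review, that EM1 and EM2 fall at comparable times.
2. Label within-group, EM3, subscale and regression results exploratory, and report them with confidence intervals.
3. State one success rule. If a single verdict of effectiveness may rest on either scale, test the two contrasts with Holm at overall two-sided 0.05. Otherwise state that both must succeed, or that each hypothesis is a separate claim with no overall verdict.

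The change takes a few sentences and alters no data collection. The cost is power. Under Holm, the unadjusted between-group test at d=0.5 with 17 per arm falls from about 0.29 to 0.20 at the first step, a loss of roughly a third. Baseline adjustment recovers part of this (0.27 at an assumed baseline–outcome correlation of 0.5) and more if that correlation is higher. The both-must-succeed rule avoids splitting alpha but lowers the chance of overall success. The separate-claims rule costs no power but gives up the single verdict. Low between-group power at this sample size remains under every option, and the report should say so.
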